# Implementing work-related Mental health guidelines in general PRacticE (IMPRovE): a protocol for a hybrid III parallel cluster randomised controlled trial

**DOI:** 10.1186/s13012-021-01146-8

**Published:** 2021-08-04

**Keywords:** Guideline implementation, General practice, Hybrid III trial, Mental health, Work, Integrated Knowledge Translation

## Abstract

**Background:**

The Clinical Guideline for the Diagnosis and Management of Work-related Mental Health Conditions in General Practice (the Guideline) was published in 2019. The objective of this trial is to implement the Guideline in general practice.

**Trial design:**

Implementing work-related Mental health conditions in general PRacticE is a hybrid III, parallel cluster randomised controlled trial undertaken in Australia. Its primary aim is to assess the effectiveness of a complex intervention on the implementation of the Guideline in general practice. Secondary aims are to assess patient health and work outcomes, to evaluate the cost-effectiveness of the trial, and to develop a plan for sustainability.

**Methods:**

A total of 86 GP clusters will be randomly allocated either to the intervention arm, where they will receive a complex intervention comprising academic detailing, enrolment in a community of practice and resources, or to the control arm, where they will not receive the intervention. GP guideline concordance will be assessed at baseline and 9 months using virtual simulated patient scenarios. Patients who meet the eligibility criteria (>18years, employed, and receiving care from a participating GP for a suspected or confirmed work-related mental health condition) will be invited to complete surveys about their health and work participation and provide access to their health service use data. Data on health service use and work participation compensation claim data will be combined with measures of guideline concordance and patient outcomes to inform an economic evaluation. A realist evaluation will be conducted to inform the development of a plan for sustainability.

**Results:**

We anticipate that GPs who receive the intervention will have higher guideline concordance than GPs in the control group. We also anticipate that higher concordance will translate to better health and return-to-work outcomes for patients, as well as cost-savings to society.

**Conclusions:**

The trial builds on a body of work defining the role of GPs in compensable injury, exploring their concerns, and developing evidence-based guidelines to address them. Implementation of these guidelines has the potential to deliver improvements in GP care, patient health, and return-to-work outcomes.

**Trial registration:**

ACTRN12620001163998, November 2020

**Supplementary Information:**

The online version contains supplementary material available at 10.1186/s13012-021-01146-8.

Contributions to the literature* An intervention that implements an evidence-based clinical guideline equipping GPs with recommendations, resources, and networks to improve GP care.
Improvements in GP care that enhance patient recovery, work productivity, and reduce health service utilisation and compensation claims.A demonstration of how researchers and policy makers can work with GPs to facilitate the translation of research into clinical practice.Rigorous evaluation processes and measurable feasibility and economic value mean more compensation partners can nationally roll out the intervention.

## Background

Mental health conditions that have arisen as a result of work factors (henceforth referred to as work-related mental health conditions) are one of the most challenging injuries to manage [1, 2]. These conditions can result in some of the most expensive and complex claims and afflicted patients can take three times longer to return to work compared with the median time for all claims [3].

GPs play a key role in the diagnosis, treatment, and care of patients with work-related injuries. They are perceived as one of the most trusted sources of advice for patients, considered by patients and other health professionals to be the primary coordinator of patient care, and are often tasked with advocating to employers on the patient’s behalf [2, 4, 5]. Yet, many GPs, internationally, describe substantial challenges in providing this care, particularly where the injury involves a mental health condition [4–9]. For instance, GPs describe difficulty diagnosing mental health conditions and determining the work-relatedness of a mental health condition, navigating system complexities, coordinating clinical care, communicating with workplaces, concern about imposing further harm on the patient (for instance concern about the patient facing stigma at work if they are known to have a work-related mental health condition), and a lack of evidence about optimal clinical practice [5, 8, 10, 11]. That similar challenges are described internationally underscores that across the compensable injury landscape, patients with mental health conditions that have arisen from work are seen as difficult to manage, and that GPs are fundamental to brokering improved health and employment outcomes for such patients. The nature of these challenges suggests that they can be overcome through interventions that improve knowledge and offer GPs the opportunity to grow their confidence and skills in providing care.

In 2019, an evidence-based clinical guideline titled *Clinical guideline for the diagnosis and management of work-related mental health conditions in general practice* was published [12]. This guideline is the only GP-focused guideline on diagnosing and managing work-related mental health conditions internationally. It was developed according to the gold-standard for guideline development in Australia—and approved by the National Health and Medical Research Council—and is endorsed by the two peak general practice membership organisations in Australia, the Royal Australian College of General Practitioners and the Australian College of Rural and Remote Medicine. It addresses specific clinical dilemmas about the diagnosis and management of work-related mental health conditions that have been raised by GPs and other clinical and policy stakeholders [11, 13].

Despite the Guideline being available, it is widely recognised that clinicians seldom consult clinical guidelines when making clinical decisions [14]. Instead, they more often develop internalised, tacit protocols that are based on collective reinforcement by peers, previous clinical experiences, and, to a lesser extent, literature or guidelines [14]. To effectively embed guideline-concordant behaviour into practice, an intervention would need to facilitate the development of new collectively reinforced, internalised tacit beliefs that align with the Guideline recommendations and overcome the concerns described by GPs. These requirements align well to the constructs of normalisation process theory: coherence, cognitive participation, collective action, and reflexive monitoring [15]. Therefore, an intervention that operationalizes normalisation process theory and re-enforces the role of peers and opinion leaders [16, 17] may be effective at implementing the Guideline. Whilst these factors ready a clinician for behaviour change, the application, practice, and embedding of new practices occurs over time and stages [18]. As such, a combination of these elements may provide an effective and sustainable model for influencing guideline-concordant behaviour change in GPs.

Two intervention approaches that encompass the principles of normalisation process theory and the influence of peers and opinion leaders are academic detailing and communities of practice. These interventions have some success in changing GP behaviour when offered individually [19–22], but are more effective when offered together [19, 23]. Academic detailing involves peer-to-peer delivery of evidence-based key messages that are tailored to the needs of participating clinicians [20, 21, 23]. Academic detailing has been used regularly to educate clinicians and facilitate evidence-based practice [24].

Additionally, a community of practice involves driving innovation and excellence through sustained interaction over a period of time [22, 25]. Communities of practices have been used successfully in Australia to improve evidence-based care and communication skills in general practice [26]. They provide support for practitioners who can feel isolated in dealing with clinical problems, helping them to create networks and implement new models of care [27]. A third approach, the provision of resources to support guideline implementation, is also more effective when combined with peer-to-peer strategies [28].

Our complex intervention combines these academic detailing a community of practice and the provision of resources and is expected to facilitate guideline implementation by introducing these in a staged manner to facilitate guideline-concordant practice over time (Figure 1). It will do so in the following ways: (a) addressing professional isolation; (b) learning from respected peers; (c) enabling GPs to demonstrate their own leadership by assisting their peers; (d) enabling GPs to develop confidence in their plan of action before consulting with the patient, or stakeholder involved in the patient’s care; and (e) providing this interaction in a flexible environment that caters to the GP’s resource availability (e.g. time, mode of communication).

**Fig. 1 Fig1:**
[figure not shown]
Theoretical basis for the IMPRovE intervention based on Prochaska and DiClemente Transtheoretical Model of Change [18]

## Research hypothesis

Our primary hypothesis is that exposure to a complex intervention consisting of academic detailing, and provision of resources and engagement in a digital community of practice will increase the delivery of guideline-concordant care by GPs to patients regarding the diagnosis and management of work-related mental health conditions. We hypothesise that increases in guideline-concordant care will translate into improvements in health status and work productivity, and reductions in health service utilisation.

## Aims

This study aims to assess the effectiveness of a complex intervention involving academic detailing, provision of resources, and engagement in a digital community of practice on the implementation of evidence-based guidelines for the diagnosis and management of work-related mental health conditions in general practice. Our secondary aims are to (a) improve the health and return-to-work outcomes for patients with work-related mental health conditions in this study, (b) evaluate the cost-effectiveness of the guideline implementation strategy, and (c) develop an implementation plan for sustainability.

## Methods

### Design

Implementing work-related Mental health conditions in general PRacticE (IMPRovE) is a hybrid III parallel cluster randomised controlled trial (RCT) of a complex intervention that involves receipt of academic detailing, enrolment onto a digital community of practice, and access to a library of resources to support guideline implementation. GP clinics (clusters) will be randomised to either intervention or control. A cluster design was chosen to avoid confounding that could arise if participating GPs from a single clinic were allocated to different arms of the trial. Participating GPs in clinics assigned to the intervention arm will receive the intervention. GPs in the control arm will not receive the intervention. Patients will be recruited to each arm (Figure 2).

**Fig. 2 Fig2:**
[figure not shown]
CONSORT flowchart for the IMPRovE trial design and outcomes. *Patient numbers calculated assuming 25% of GPs will drop out of study. **GP guideline concordance calculated assuming 25% of GPs will drop out of the study

As a hybrid III trial [29], the primary outcome of the trial will demonstrate the effectiveness of this complex intervention to improve guideline concordance by GPs. The secondary outcomes of the trial will demonstrative the effectiveness of the complex intervention on patient heath status and cost-effectiveness. Lastly, we will review the likelihood of this intervention being sustained and develop a plan for sustainability. This protocol has been reported according to the Template for Intervention Description and Replication (TIDieR) checklist [30] and the CONSORT extension for Cluster Trials [31] (Additional files 1 and 2, respectively).

### Setting

The study will be conducted across all states and territories in Australia. Recruitment of GPs will occur from December 2020 until December 2021 whilst recruitment of patients will occur from February 2021 until September 2022 or the latest date representing nine-months after the final GP provides baseline measures.

### Inclusion and exclusion criteria

#### General practitioners

GPs are eligible to participate if they can recruit 7 to 24 eligible patients over the course of the trial. GPs may consent after their practice has already been randomised; however, we will aim to enrol all GPs before their practice has been notified of their allocation. If a GP works across multiple sites, then we will randomise both sites together.

#### Patients

Patients are eligible if they are 18 years or older, have a confirmed or suspected work-related mental health condition, are receiving care from a participating GP, and are employed at the time of enrolment. Patients who are employed but are not working (e.g. on paid or unpaid leave) and those who have an active workers’ compensation claim are also eligible to participate in the study.

### Participant recruitment

#### General practitioners

GPs meeting the minimum caseload requirements for eligibility will be recruited through regional health authorities (known as primary health networks), GP membership organisations, study partners, and other relevant healthcare organisations using newsletters, website updates, and social media avenues.

#### Patients

Patients will be recruited via the participating clinic through advertisement in the clinic waiting room, advertisement on the participating GP’s desk, or directly through the participating GP, who will identify eligible patients and provide these patients with a printed information pack about the study. The information pack will include an explanatory statement, consent forms, and a reply-paid envelope. In addition to seeking consent to participate in data collection, consent will also be requested from patients to access administrative records of their health service utilisation for the purposes of an economic evaluation. Patients who wish to participate in the study will be invited to contact the IMPRovE project team for further information or to return their completed consent forms directly to the team using the reply-paid envelope.

### Sample size

A sample size of 86 clinics (clusters), with a minimum of one GP per cluster and assuming a GP dropout rate of 25%, has >80% power to detect a medium-large effect size of Cohen’s d of 0.69 (assuming a GP-level outcome score change of 1.2 on a scale with score range of 0 to 9 and a standard deviation of 1.75 as identified in a pilot study of the primary outcome tool; correlation between baseline and follow-up measurements of 0.3, and two-sided significance of 0.05).

We estimate that each GP cluster will recruit a minimum of 7 and a maximum of 24 patients (the cut-off to ensure that the patient sample is not skewed by a high-recruiting cluster) over the study period. Based on our analysis of high-caseload GPs [32], we estimate that there will be approximately 22 eligible patients/year/GP. Accounting for a 66% estimated rate of refusal to participate as observed in another study that recruited participants with mental health conditions in the Australian general practice setting [33], we estimate that at least 7 eligible patients will be successfully recruited by each participating GP in a 9-month period.

We anticipate that approximately 448 patients who are recruited within the 9 months (224 from control clinics and 224 test clinics; 7 per clinic/cluster) will have 3-month data. These patient numbers assume up to 25% of the 86 recruited GPs will drop out of the study. Using data from these patients, we will have 90% power to detect medium effects (Cohen’s d = 0.5) in secondary outcome measures between two groups (test/control) at 3 months. Calculations assume an alpha of 0.01, ICC of 0.03, and correlation of 0.5 between individual scores. Calculations were made using Cluster statistical software [34].

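### The plan's own inputs give about 5.6 recruited patients per GP in 9 months, not at least 7, so the 448 patients are overstated by about 25%; the 90% power claim is not reproduced but is conservative

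*Protocol article*

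**What the plan says.** All the relevant figures are in the protocol article, Sample size section.

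- Supply of patients: "we estimate that there will be approximately 22 eligible patients/year/GP".
- Consent: "Accounting for a 66% estimated rate of refusal to participate".
- Resulting yield: "we estimate that at least 7 eligible patients will be successfully recruited by each participating GP in a 9-month period".
- Clusters: "A sample size of 86 clinics (clusters), with a minimum of one GP per cluster".
- GP loss: "These patient numbers assume up to 25% of the 86 recruited GPs will drop out of the study".
- Patient total: about 448, or 224 per arm at 7 per cluster. They are described as recruited within the 9 months and as all having 3-month data.
- Power: "we will have 90% power to detect medium effects", with d = 0.5, alpha 0.01, ICC 0.03 and a correlation of 0.5 between individual scores.

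Two other places bear on the point. The GP inclusion criterion reads "GPs are eligible to participate if they can recruit 7 to 24 eligible patients over the course of the trial". The Setting section has GPs enrolling from December 2020 to December 2021. Patients are recruited from February 2021 to September 2022, or to nine months after the last GP's baseline.

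**The concern.** The supply of patients is a rate per year, but the yield is claimed for nine months. Nothing in the section scales one to the other, and the claimed 7 is close to what the inputs give over a full year. The 7 is also presented as a floor, whereas the inputs yield an average.

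The figure carries forward. It produces the 448 patients on which the secondary-outcome power rests, and the patient-level QALY analysis draws on the same sample. The only losses named on the way to 448 are refusal by patients and dropout of GPs, so the number recruited and the number with 3-month data are the same. If the count is wrong, recruitment will be judged against a 9-month expectation that the plan's own inputs do not support, and the power statement will be attached to the wrong number.

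**Working it through.** **Step 1. Yield per GP.** Inputs: 22 eligible per year, 66% refusal (34% consent), 9 months. Assumption: even accrual over the year.

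- 12 months: 22 × 0.34 = 7.48
- 9 months: 7.48 × 9/12 = 5.61
- Time to reach 7: 12 × 7 / 7.48 = 11.2 months
- Supply needed for 7 in 9 months: 7 / (0.34 × 0.75) = 27.5 eligible patients per year. Alternatively, refusal of 1 − 7 / (22 × 0.75) = 58%. The section states neither.

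**Step 2. Patient total.** 86 × 0.75 = 64.5 clusters. The plan's figure is reproduced with 64 clusters: 64 × 7 = 448, or 224 per arm. With the 9-month yield, 64 × 5.61 = 359 (362 with 64.5 clusters). The ratio is 448 / 359 = 1.25. Since 64 × 7 already equals 448, nothing has been taken off for patients lost before 3 months.

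**Step 3. Power.** Sidedness is not stated for this calculation, so two-sided alpha 0.01 is assumed (critical value 2.576), with SD 1, d = 0.5 and 32 clusters per arm. Design effect = 1 + (m − 1) × 0.03, and power = Φ(0.5 / √(2 × design effect / n per arm) − 2.576).

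- 448 patients: m = 7, design effect 1.18, n = 224 per arm. 0.5 / √(2 × 1.18 / 224) = 4.87; Φ(4.87 − 2.576) = 98.9%.
- 359 patients: m = 5.61, design effect 1.138, n = 179.5 per arm. Power = 96.9%.

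A t-based version with 62 degrees of freedom gives 98.5% and 95.9%. One-sided alpha gives 99.5% and 98.3%. At r = 0.5 a change score has the same variance as a post score, 2 × (1 − 0.5) = 1, so these figures serve for both. ANCOVA with r = 0.5 multiplies the variance by 1 − 0.25 = 0.75. None of these variants returns 90%; all are higher.

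**Step 4. Allowing for patient loss.** The article gives no rate, so a range is assumed.

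| Patients with 3-month data | Basis | No baseline adjustment | ANCOVA, r = 0.5 |
|---|---|---|---|
| 448 | 64 × 7 | 98.9% | 99.9% |
| 359 | 64 × 5.61 | 96.9% | 99.5% |
| 323 | 359, 10% lost | 95.2% | 99.0% |
| 287 | 359, 20% lost | 92.7% | 98.1% |
| 251 | 359, 30% lost | 89.0% | 96.5% |
| 215 | 359, 40% lost | 83.4% | 93.6% |

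With 32 clusters per arm, 90% power needs about 260 patients with 3-month data without baseline adjustment (260 / 359 = 72%), or about 190 with ANCOVA (189 / 359 = 53%).

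**The case against.** **The 22 may not be new patients arriving evenly.** Eligibility covers anyone employed and under a participating GP's care. If the 22 are distinct people seen in a year and many attend repeatedly, more than three quarters of them would be seen in nine months, and the yield would lie between 5.6 and 7.5. That is possible, and it is why even accrual is stated as an assumption. But the section does not say this, and it would not turn an average into a floor.

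**Recruitment lasts longer than nine months.** This largely stands for the trial as a whole. On the Setting dates, a GP enrolled in mid-2021 has about 15 months (7.48 × 15/12 = 9.4 patients); only the last-enrolled GPs are held to about nine. A reader might infer that the trial could never expect to reach 448. The documents do not support that. What fails is the 9-month basis to which the 448 is expressly tied.

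**Clinics may have several GPs.** One per cluster is a minimum, so some clinics could exceed 7. However, the yield is stated per GP, and no larger number of GPs enters the 448.

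**The GP minimum of 7.** A reader might infer that a typical GP would fail the eligibility criterion. The 7 to 24 range applies over the course of the trial, not over nine months, so it is not contradicted.

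**Power remains adequate.** This stands in full. A power statement that is not reproduced can be read as a shortfall; here the discrepancy runs the other way.

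**Conclusion.** The point holds as an error in stated sample-size figures, not as a threat to the trial's power. With even accrual, the plan's inputs give 5.6 patients per GP in nine months and about 359 in total, so 448 is about 25% too high for the window it names. No patient loss before 3 months is allowed for. The stated 90% does not match the stated inputs, which give about 99% with 448 patients and about 97% with 359.

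The 90% claim therefore survives the correction. From 359 recruited, it is lost only beyond about 28% patient loss without baseline adjustment, or about 47% with ANCOVA at r = 0.5. These limits rest on two-sided alpha 0.01, ICC 0.03 and a normal approximation; the t-based figures are slightly lower.

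The outcomes concerned are secondary, and the GP-level primary calculation does not use the patient count. This should be fixed, but it does not put the design in question.

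**What to change.** In the Sample size section:

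1. Either restate the expectation as about 5.6 patients per GP and about 359 patients in nine months, or keep 7 per GP and give the window as about 11 to 12 months. The Setting dates allow the longer window for most GPs but not the last enrolled, and the text should say so. If the 22 per year is meant in a way that supports a higher 9-month yield, explain it.
2. State an assumed patient retention to 3 months, and separate the number recruited from the number with 3-month data.
3. Restate power for the resulting number, giving sidedness and how the 0.5 correlation enters. The requirement for 90% at d = 0.5 depends on that choice (about 260 patients without baseline adjustment, about 190 with ANCOVA), so neither should be given without its method.

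The GP eligibility range of 7 to 24 over the trial and the primary sample size need not change. The cost is a few corrected sentences; no additional patients or clinics are required.
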